### Blinding

Those delivering interventions cannot be blinded to group allocation. Participants, assessors, and statisticians will be blinded throughout the entire trial period. Assessors are independent research assistants who are not involved in intervention delivery. Intervention providers are asked to not disclose group assignment to participants and assessors such as not talking about the mHealth intervention. Statisticians will receive data with unlabeled group coding and labels will only be revealed after completion of statistical analyses and start of interpretation of results.

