#### Intervention design and strategy

The intervention group will receive intervention for the first 6 months after recruitment into the study. In the second 6 months, instructed intervention will be terminated, but self-management of lifestyles can continue based upon participants’ decision and quarterly assessment will continue to observe participants’ maintenance of healthy lifestyles.

According to the 3SLIFE, interventions will take place at three levels: (1) individual level (microsystem): providing medical consultation services and health knowledge, one-to-one health coaching, and requiring participants’ voluntarily documentation of their daily lifestyles; (2) family level (mesosystem): communicating with family members about participants’ lifestyle status, making healthy lifestyle improvement plans with family members, and improving participants’ self-management ability through family supervision; (3) community level (macrosystem): organizing online and offline community activities, creating healthy environments, and improving self-management ability of healthy lifestyles through online healthy lifestyle documentation and offline community activities.

The control group will receive placebo interventions unrelated to healthy lifestyles and chronic disease risk factors (e.g., information about the hospital visit process) for the first 6 months after enrollment. Participants in control group will also complete quarterly assessment. In the second six months, the placebo interventions will be terminated while quarterly assessments continue. To ensure that the control group can benefit from the same healthy lifestyle interventions, all participants in the control group will have access to the same program as the intervention group at the end of the trial followed up with assessments as previously given provision of consent.

More details of intervention strategies are listed [32], in Table 1 and Fig. 2 according to the TIDieR framework [32].

**Table 1 Tab1:** Intervention strategies for control and intervention groups

	Control group	Intervention group

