**Individual**		
Intervention	**·**Content: Providing medical consultation services and knowledge unrelated to healthy lifestyles (e.g., hospital treatment procedures) **·**Material: Homemade videos or weblinks to videos, and pictures **·**Provider: Group manager **·**Where: WeChat group **·**Schedule: For 6 months. Providing topics unrelated to healthy lifestyles twice a week	**Knowledge:** **·**Content: Providing medical consultation services and regular daily health knowledge related to healthy lifestyles and other topics (e.g., hospital treatment procedure) **·**Target: Changing misconceptions about healthy lifestyles; increasing knowledge about healthy lifestyles **·**Material: Homemade videos or weblinks to videos, and pictures **·**Provider: Group manager **·**Where: WeChat group **·**Schedule: For 6 months, providing topics related to healthy lifestyle once a day, and providing topics unrelated to healthy lifestyles twice a week **Skill:** **·**Content: One-on-one health coaching **·**Target: Guiding changes in unhealthy lifestyle; guiding engagement in healthy lifestyles; providing skills in maintaining healthy lifestyles **·**Materials: Live streaming platform, online course (e.g., exercise, diet), recipe (guided by the Mediterranean diet), tools (e.g., fitness aids such as elastic bands, medication aids) **·**Provider: Health professor, group manager **·**Where: WeChat and Tiktok live streaming platform, and homemade videos **·**Schedule: Being scheduled for 6 months. Live classes are offered twice a week; daily recipe and daily exercise guidance were provided
Self-management	None	**Empowerment:** **·**Content: Participants’ voluntarily online documentation of their daily lifestyle **·**Target: Self-management of health lifestyles with encouragement, self-supervision, and supervision from others **·**Materials: Gift (household goods) **·**Where: WeChat and offline activities **·**Provider: Group manager **·**Schedule: Inviting all participants document daily lifestyles (scheduled for 12 months) One-to-one online communication once a week to remind unhealthy lifestyle modification or healthy lifestyle maintenance (within 6 months). Being awarded with gifts consisting of daily necessities (e.g., soap and laundry detergent) for participants who document lifestyles well for that month in monthly offline activity (within 6 months)

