**Fig. 3 Fig3:**
[figure not shown]
SPIRIT flow diagram for the schedule of enrolment, interventions, and assessments. FFQ, Food Frequency Questionnaire; IPAQ, short version of the International Physical Activity Questionnaire; PSQI, Pittsburgh Sleep Quality Index; GAD-7, 7-item scale for General Anxiety Disorder; PHQ-9, patient health questionnaire depression module; mGSES, modified General Self-Efficacy Scale; MoCA-B, Montreal Cognitive Assessment, Basic Version; mMSPSS, modified Multidimensional Scale of Perceived Social Support; SPPB: Short Physical Performance Battery; PWV, pulse wave velocity; QCT: Quantitative Computed Tomography; BMD: bone mineral density; CTA: computed tomography angiography. ^a^Blinding of participants, assessors, and statisticians. ^b^Body circumference included neck, waist, belly, hip, arm and leg circumference. ^c^SPPB included feet together test, semi-tandem stand test, tandem stand test, 4-m walk test, and five times sit-to-stand test. ^d^Color doppler ultrasonography included abdominal, carotid and cardiac ultrasonography. ^e^Blood tests include total white blood cell count (WBC), red blood cells (RBC), haemoglobin (HGB), platelets (PLT), lymphocytes, monocytes, neutrophils, eosinophils, fasting blood glucose fasting blood glucose (FBG), triglycerides (TG), cholesterol (CHOL), high-density lipoprotein cholesterol (HDL-CH) and low-density lipoprotein cholesterol (LDL-CH), total protein (TP), albumin, globulin, alanine transaminase (ALT), aspartate amino transferase (AST), gamma-glutamyl transpeptidase (GGT), Creatinine (Cr), urea, uric acid (UA) and C-reactive protein (CRP). ^f^Including metagenomics and metabolomics. X The item will be surveyed implemented or on relevant time point.

The item will be implemented in the relevant time period.

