### Ethics approval, protocol amendments and consent

This trial will be conducted in compliance with the study protocol, the Declaration of Helsinki, and good clinical practice. Ethical approval for this study has been obtained from the Ethics Committee of the West China School of Public Health and West China Fourth Hospital (Gwll2022096).

The trial has been registered with the Chinese Clinical Trials Registry (ChiCTR2300070575, https://www.chictr.org.cn/index.aspx). The design and implementation of this cluster-RCT is in line with the extension of the SPIRIT 2013 statement [31], and reporting of the trial will be conducted according to the CONSORT statement [64].

Prior to participation, interested participants will be provided with a written informed consent form that includes details of the trial, an explanation of potential risks and benefits, and contact information for study members. Participants may choose not to participate in this study or request to withdraw from the study at any time by notifying the investigator, and any rights of the withdrawing person will not be affected as a result. The investigator may terminate a subject's continued participation in this study if the subject does not comply with the study plan, or if a study-related injury occurs.

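### Participants are declared blinded throughout, but intervention participants must know they are being coached, and four of the five primary components are their own reports

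*Protocol article*

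**What the plan says.** The Blinding section of the protocol article accepts that those delivering the interventions cannot be blinded, then says: "Participants, assessors, and statisticians will be blinded throughout the entire trial period". Footnote a of Fig. 3 repeats this: "Blinding of participants, assessors, and statisticians". The only means given for keeping participants blinded is in the same section: "Intervention providers are asked to not disclose group assignment to participants and assessors such as not talking about the mHealth intervention".

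Table 1 sets out what each arm receives. Under individual-level knowledge the intervention arm has: "For 6 months, providing topics related to healthy lifestyle once a day, and providing topics unrelated to healthy lifestyles twice a week". It also has live classes twice a week, daily recipes and exercise guidance, weekly one-to-one contact about lifestyle change, monthly gifts for good lifestyle documentation, and gifts for improved health status. For the other arm, Intervention design and strategy says: "The control group will receive placebo interventions unrelated to healthy lifestyles and chronic disease risk factors". Table 1 lists no self-management element for controls at the individual, family or community level.

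Primary outcomes defines success as at least one fewer unhealthy lifestyle at six months. According to Table 2, smoking, alcohol, physical activity and diet come from questionnaires, and overweight/obesity comes from a medical examination.

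**The concern.** A person who is taught, reminded and rewarded for changing lifestyle knows what is being delivered. The stated safeguard asks providers to keep silent about an intervention that consists largely of their talking to participants. The protocol therefore claims a property that the design lacks in at least one arm.

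This matters because of the endpoint. Assessor blinding protects little when the participant is the source of the data. Participants who know they were coached may report improvement more readily than controls, and a single reported improvement turns an unfavourable outcome into a favourable one. A reader who relies on the blinding statement would rate this bias as low.

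The Discussion names recall bias and socially desirable answering as limitations, but does not say that either could differ between arms. One mitigation offered there, documentation records as a recall aid, may itself be uneven, since Table 1 schedules daily lifestyle documentation for the intervention arm only.

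**Working it through.** **Step 1: the blinding statement against the arm content.**

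- Intervention arm: openly about lifestyle, every day for six months, with personal contact each week and rewards tied to lifestyle documentation. Awareness of receiving a lifestyle programme is unavoidable.
- Control arm: a WeChat group, a group manager, consultation services, monthly offline activities and quarterly consultations, on topics other than lifestyle. Controls' lifestyles are assessed quarterly. They may or may not realise that another package exists.
- Safeguard: a request to providers. It could limit what controls hear about the other package. It cannot hide the programme from those receiving it.

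**Step 2: exposure of the endpoint.** Four of the five components are reported by the participant and one is measured. A change in one component suffices.

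**Step 3: the plan's own sample size.** Sample size gives 2% versus 12%, alpha 0.05, power 0.80, a chi-squared test, 102 per group, and 128 per group after 20% attrition. With the pooled two-sided formula and a mean proportion of 0.07:

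n = [1.960 × √(2 × 0.07 × 0.93) + 0.842 × √(0.02 × 0.98 + 0.12 × 0.88)]² / 0.10²
= (0.7072 + 0.2978)² / 0.01 = 101.005, rounded up to 102.

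102 / 0.80 = 127.5, rounded up to 128. Both figures reproduce. The blinding point changes no design figure.

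**Step 4: illustration of what differential reporting could do.** The over-reporting rates are assumptions; the documents give none. Suppose no true effect and a 2% favourable rate in both arms. Let a share *m* of the participants who are really unfavourable report one improvement. The observed rate in that arm becomes 0.02 + 0.98 × *m*. The table gives the exact probability that the uncorrected two-sided chi-squared test is significant, with 102 per arm and clustering ignored.

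| Over-reporting, control | Over-reporting, intervention | Observed rates | Apparent risk ratio | Probability of significance |
|---|---|---|---|---|
| 0% | 0% | 2.0% vs 2.0% | 1.0 | 4% |
| 0% | 3% | 2.0% vs 4.9% | 2.5 | 18% |
| 0% | 5% | 2.0% vs 6.9% | 3.5 | 38% |
| 0% | 10% | 2.0% vs 11.8% | 5.9 | 83% |
| 3% | 5% | 4.9% vs 6.9% | 1.4 | 9% |
| 3% | 10% | 4.9% vs 11.8% | 2.4 | 44% |
| 5% | 10% | 6.9% vs 11.8% | 1.7 | 23% |

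The planned risk ratio is 12% / 2% = 6. The result is sensitive because the assumed control rate is so low: a few false improvements per hundred in one arm are large relative to 2%. Over-reporting in both arms weakens the effect considerably.

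**The case against.** Much can be said for the plan. The control arm is an attention-type placebo with matching channels and contacts, all participants in a village share one arm, and included villages lie at least 2 km apart. Controls may well not know that theirs is the comparison package. Baseline data are collected before randomization, assessors take no part in delivery, and the Discussion says that face-to-face data collection takes place in a private room. The Discussion also concedes reporting bias openly. This stands, and it is why the claim cannot be called impossible for controls. It does not rescue the claim for the intervention arm, and awareness there is enough for one-sided reporting.

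A reader might also infer that the consent process unblinds everyone, since "interested participants will be provided with a written informed consent form that includes details of the trial". The form is not shown, and the article does not say that it describes both arms, so this is not established.

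A reader might likewise infer that controls are unblinded by the promise that "all participants in the control group will have access to the same program as the intervention group at the end of the trial". That access comes after the six- and twelve-month assessments. It could matter only if announced earlier, and the article does not say that it is.

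Finally, the over-reporting rates are hypothetical, and the planned analysis is a mixed-effects Poisson model, not an unclustered chi-squared test. That is correct: the figures show sensitivity and predict nothing.

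**Conclusion.** The concern holds, on arm content alone. The statement that participants are blinded is wrong for the intervention arm and not assured for controls. With four of five primary components self-reported, a positive primary result cannot be presented as protected from reporting that differs by arm.

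The possible size is substantial but unknown. Under the stated assumptions, the chance of a spurious significant result runs from about 18% to 83% when 3% to 10% over-report in the intervention arm only. With 3% over-reporting in controls it is about 9% to 44% for intervention-arm rates of 5% to 10%. The documents do not support the stronger readings that the trial will be biased by any given amount, or that controls necessarily know their allocation. The sample size is unaffected. The correction is one of wording and interpretation, and it should be made because it changes what a positive result can be said to show.

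**What to change.** 1. In the Blinding section and footnote a of Fig. 3, limit the claim to assessors and statisticians. State that participants are not blinded, and that controls may at most be unaware of the alternative package.
2. In the Discussion, extend the limitation on recall and socially desirable answers to say that reporting may differ by allocation.
3. Present the six-month results for the individual components beside the primary result as supportive evidence, with examined BMI shown apart from the four self-reported components. Secondary outcomes already lists the specific lifestyles, including BMI, at six months, so this is a matter of presentation. Interpret an effect carried only by self-reported components as change in reported lifestyle.

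The cost is protocol wording and one arrangement of planned results, with no new data. The downsides are a less favourable blinding statement and few events for the BMI component, which can therefore support the primary result but not replace it.

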### Sample size

The primary outcome is the improvement of modifiable unhealthy lifestyles, with a reduction by at least one unhealthy lifestyle at 6 months considered a favorable outcome (coded 1) and any other outcome unfavorable (coded 0). According to a previous study, the prevalence of at least one unhealthy lifestyle in Chinese community residents is 89.6% [2, 37]. According to an analysis of the previous two survey waves of the CMEC, it is expected that 2 percent of the control group participants will achieve a favorable outcome. We assume that a 10% percent increase of participants with favorable outcome in the intervention group (to 12% in total) constitutes a minimally important difference.

To achieve a power *of* 0.80 to obtain a statistically significant signal at α <  = 0.05 for p_1_ = 0.02 vs. p_2_ = 0.12 with a chi-squared test of independence, the sample size is estimated as 204 (102 per group). To account for participant attrition of estimated 20%, recruitment target is 128 participants per group, with a total sample of 256 participants for assessment and evaluation.

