#### Participants

##### Inclusion criteria

Being 18 years old or above;Having participated in two survey waves of the CMEC;Having access to the internet via a smartphone.

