##### Exclusion criteria

Having a history of major psychiatric illnesses (e.g., schizophrenia and bipolar disorder), Parkinson’s disease, severe cognitive or hearing impairment according to medical records obtained from Sichuan Medical Insurance Bureau.Having had major surgery in the past year;Receiving cancer treatment;Pregnant.

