#### Primary outcomes

The primary outcome is the reduction of modifiable unhealthy lifestyles immediately after intervention (6 months). Unhealthy lifestyles considered comprise smoking, excess alcohol consumption, physical inactivity, unbalanced diet, and overweight/obesity (representing balance between energy intake and energy expenditure). Items as formulated in the Healthy Lifestyle Index Score (HLIS) from the European Prospective Investigation into Cancer and Nutrition cohort study [41], will be used to measure these lifestyles (see Table 2). Assessment of body mass index (BMI) and categorization into overweight/obesity will rely on relevant recommendations according to Chinese guidelines [42], while dietary index is based on the Mediterranean Diet Score [43]. For reasons of simplicity each lifestyle will be coded as a dichotomous variable with 0 indicating absence, 1 indicating presence of a particular unhealthy lifestyle. The decrease of unhealthy lifestyles by at least one at 6 months is considered favorable.

**Table 2 Tab2:** Components of lifestyle risk score

Components	Score	Measurement	Definitions in the study
Smoking status	0–4	Questionnaire • History of smoking in the past	Never = 4, ex-smokers quit > 10 years = 3, ex-smokers quit ≤ 10 years = 2, current ≤ 15 cigarettes/day = 1, current > 15 cigarettes/day = 0 [41]
Alcohol intake	0–4	Questionnaire • Alcoholic beverage consumption per day	low consumption of alcohol (< 6.0 g/day = 4, 6.0–11.9 g/day = 3, 12.0–23.9 g/day = 2, 24.0–59.9 g/day = 1, 60 + g/day = 0) [41, 44]
Physical activity	0–4	International Physical Activity Questionnaire • Number of hours per week spent in moderate to vigorous activities, vigorous-intensity PA	Metabolic equivalent tasks for four activity domains (occupational PA; transportation PA; PA for housework; sports and leisure-time PA): fifth quintile = 4, fourth quintile = 3, third quintile = 2, second quintile = 1, first quintile = 0 [41]
Dietary factors	0–4	Food Frequency Questionnaire • MDS, a linear score that incorporates 9 nutritional components of the Mediterranean diet [45]	Scoring 4 to 0 points for top to bottom quintile of the MDS: fifth quintile = 4, fourth quintile = 3, third quintile = 2, second quintile = 1, first quintile = 0 [44]
Overweight/obesity	0–4	Medical examination • BMI	< 22 = 4, 22–23.9 = 3, 24–25.9 = 2, 26–27.9 = 1, ≥ 28 = 0 [46]
Total score	0–20	Total of unweighted five components	

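### Residents with no unhealthy lifestyle at baseline may enrol but cannot reach the primary outcome, and the primary model has no baseline-count term

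*Protocol article*

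**What the plan says.** The participant inclusion criteria in the Protocol article are "Being 18 years old or above;Having participated in two survey waves of the CMEC;Having access to the internet via a smartphone". The exclusions concern psychiatric, neurological, cognitive and hearing conditions, followed by "Having had major surgery in the past year;Receiving cancer treatment;Pregnant". The study-site criteria do not mention lifestyle status either.

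Under Primary outcomes, "each lifestyle will be coded as a dichotomous variable with 0 indicating absence, 1 indicating presence of a particular unhealthy lifestyle". There are five components, so the count runs from 0 to 5. The same section says "The decrease of unhealthy lifestyles by at least one at 6 months is considered favorable", and the Sample size section repeats the rule: a reduction of at least one is "considered a favorable outcome (coded 1) and any other outcome unfavorable (coded 0").

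The Sample size section states that "the prevalence of at least one unhealthy lifestyle in Chinese community residents is 89.6" per cent. It then takes 2% favourable in the control group, from the earlier cohort waves, against 12% in the intervention group.

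Under Data analysis, the primary model contains group, a random intercept for subject nested in village, and a fixed effect for town. Adjustment for the baseline value is specified only for the continuous secondary outcomes. The adjusted sensitivity model uses age and gender. Under Randomization and allocation concealment, the covariates named for balance are village size, mean age and sex ratio.

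**The concern.** A count of 0 cannot fall. Anyone who enters with no unhealthy lifestyle is scored unfavourable whatever happens in the following six months. This sits badly with the rest of the plan. The hypothesis is about changing unhealthy behaviours, which presupposes having one. Table 1 includes maintenance of healthy lifestyles among the purposes of the weekly contact, so a participant who succeeds at maintenance is still scored as a failure.

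The chance of success plausibly also depends on the starting count, at the least through the contrast between zero and one or more. Baseline data are collected before randomisation, so the count is available, but it is not a covariate in the primary model. At stake are the precision of the primary estimate, the interpretation of the favourable proportion, and possibly power, depending on whom the assumed rates describe.

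**Working it through.** **Inputs.** From Sample size: control rate 0.02, intervention rate 0.12, alpha 0.05 (taken as two-sided), power 0.80, chi-squared test, 20% attrition, prevalence 0.896. From Randomization and allocation concealment: 10 villages per arm. Every power figure below uses the plan's own individual-level calculation, which makes no allowance for clustering.

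**1. Reproduce the plan's figure.** With pooled variance and no continuity correction,

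n = [1.960·√(2p̄(1−p̄)) + 0.842·√(p₁(1−p₁) + p₂(1−p₂))]² / (p₂−p₁)²

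with p̄ = 0.07:
- first term 1.960 × √0.1302 = 0.707
- second term 0.842 × √0.1252 = 0.298
- n = 1.005² / 0.01 ≈ 101.0, rounded up to 102 per arm

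After attrition, 102/0.8 = 127.5, rounded up to 128 per arm (256 in total). Both figures match the plan, so the 89.6% does not enter the calculation. Power at 102 is Φ[(0.1·√102 − 0.707)/0.354] = Φ(0.856) = 80.4%.

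**2. Participants who cannot succeed.** (1 − 0.896) × 256 = 26.6, about 27 in total or 13 per arm.

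**3. Power depends on whom 2% and 12% describe.**

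- *All enrolled.* Power stays at 80.4%. The implied rates among those who can improve are 0.02/0.896 = 2.2% and 0.12/0.896 = 13.4%. Enrolling only such people at 102 per arm gives 84.9%.
- *Only those who can improve.* The rates among all enrolled become 0.02 × 0.896 = 1.79% and 0.12 × 0.896 = 10.75%, a difference of 9.0 points. Power at 102 per arm is 75.5%, and 80% would need 114 per arm (114/0.8 = 142.5, so 143 recruited). Enrolling only people who can improve keeps 80.4%.

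Range for the second reading, varying the assumed share able to improve:

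| Share able to improve | Power at 102 per arm |
|---|---|
| 95% | 0.78 |
| 89.6% | 0.755 |
| 85% | 0.73 |
| 80% | 0.70 |

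**4. Restricting the analysis set without recruiting more.** This leaves 102 × 0.896 = 91.4 per arm. Power moves from 80.4% to 80.8% on the all-enrolled reading, and from 75.5% to 75.9% on the other.

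**5. Effect on the relative risk.** With equal shares in both arms, 10.75/1.79 = 6.0 = 12/2, so nothing changes. With unequal shares and no treatment effect, the relative risk equals the ratio of the shares. Assumed shares of 94% (intervention) and 85% (control) give 0.94/0.85 = 1.11; the reverse gives 0.90.

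**The case against.** The strongest objection is to any claim of lost power. A reader might infer that the trial is underpowered at 75.5%. The Sample size section ties the 2% to control group participants, based on the cohort's two earlier waves, and calls the 12% a total. Entry requires having taken part in both waves. The natural reading is that both rates cover everyone enrolled, including people with nothing to reduce, and then planned power is intact. That stands.

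A reader might also infer that the effect estimate is diluted or biased. The plan reports a relative risk, which equal shares of such participants leave unchanged; only the absolute difference shrinks. Chance imbalance under randomisation adds variance, not systematic bias. Even the assumed 94% against 85% split moves a null relative risk only to 1.11, against a planned value of 6. The balancing list is also open-ended. All of this stands.

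Nor does the plan disregard baseline entirely. The outcome is a change from each person's own baseline, so only the covariate is missing.

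The 10.4% is borrowed from another study. The cut-points that turn each 0–4 component in Table 2 into yes/no are not stated, so the trial's own share may be higher or lower. Finally, enrolling all residents suits a community programme that also values maintenance. That justifies enrolling them, but not scoring them on an outcome they cannot reach.

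**Conclusion.** The point holds as a mismatch between eligibility and the primary outcome. The criteria admit people for whom the favourable outcome is impossible, and the coding counts them as failures in both arms. On the assumption that 89.6% applies to this sample, they number about 27 of 256. They add nothing to the primary comparison. With only 10 villages per arm and no baseline-count term, imbalance in the count contributes error that a variable already collected could reduce.

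The documents do not establish a power shortfall, a distorted relative risk or systematic bias. Power is 80.4% on the more natural reading of the assumed rates. It is 75.5% (0.78 to 0.70 for shares of 95% to 80%) only if those rates describe people who can improve. The protocol does not state the denominator explicitly, and should. The change is worth making because it is cheap and, made at entry, gives more power than the current plan on either reading.

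**What to change.** Preferred: add an inclusion criterion of at least one of the five unhealthy lifestyles at baseline. At the same sample size this gives about 85% power if 2% and 12% describe all enrolled under the current criteria, and keeps 80% if they describe people who can improve.

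Alternative, if all residents are wanted for maintenance outcomes: define the primary analysis set as all randomised participants with a baseline count of at least 1. The count is fixed before randomisation, so the intention-to-treat comparison is preserved within that set. This makes the outcome attainable for everyone analysed but gains almost no power unless more people are recruited.

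In either case:
- Add the baseline count to the primary model as one covariate. About 14 events are expected among 204 analysable participants (102 × 0.02 + 102 × 0.12 ≈ 2 + 12), so a single term is prudent.
- State which population the 2% and 12% refer to.
- State the cut-points that define each unhealthy lifestyle, since the criterion or analysis set depends on them.

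The cost is one eligibility or analysis-set line, one covariate already collected, and slightly more screening if entry is restricted. The primary result would then apply to residents with at least one unhealthy lifestyle rather than to all residents.
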